### Sample size calculation and statistical analysis

Sample size was powered to detect meaningful differences between the intervention (FSN + OSC) and control group (OSC + IPE) across six primary outcomes: 1) percent ever breastfed, 2) percent exclusively breastfed through 6 months of age, 3) mean duration of breastfeeding (at 12 months postpartum), 4) percent ever introduced sugar sweetened beverages at 12, 18 and 24 months, 5) mean score on responsive feeding scale (5-point scale – evaluated at 2, 4, 6, 9, 12, 18 and 24 months postpartum), and 6) mean BMI z-score at 24 months of age. A sample size of 338, or 169 per group, was deemed sufficient to detect meaningful differences across all outcomes, taking into account an estimated 16% loss-to-follow-up at 24 months postpartum (based on the previous FS trial) [54] and ensuring at least 80% power and significance level of 5%. Sample sizes and power were calculated using Stata 13’s power command (two means for continuous variables and two proportions for binary variables) (Table 3). The only exception among the primary outcomes was BMI z-score. Power simulation was conducted using a random draw and random treatment assignment from real site population data. The simulation varied the treatment effect and was run 10,000 times for each treatment effect level from which power was calculated. Simulation was also used to calculate power for moderator analyses. We hypothesize that maternal psychosocial factors, food/water insecurity and constrained physical activity environment will moderate the impact of the intervention on maternal feeding practices and healthy weight knowledge/behaviors. We also hypothesize that food/water insecurity and constrained physical activity could moderate the impact of improved maternal feeding practices and healthy weight behaviors on child diet and physical activity. While we will not have the power to examine interaction terms for all outcomes, we will have > 80% power to detect meaningful difference of differences in breastfeeding duration (48 days) and responsive feeding scales (0.4 to 0.6). The interaction terms for other outcomes will be explored as hypothesis generating to determine trends that would warrant further study with larger samples sizes.

**Table 3 Tab3:** Sample Size Calculations

Outcome Measures	Detectable Differences
% Mothers initiated breastfeeding	14%
% Exclusive breastfeeding through 6 months of age	15%
Mean breastfeeding duration	23 days

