% Introduced SSBs	13%
Infant/Toddler Responsive Feeding Scale:	
• Responsive • Forceful • Indulgent • Restrictive • Uninvolved	0.20 points 0.24 points 0.22 points 0.20 points 0.32 points
BMI z-score	0.33 (SDs)

Blood samples are collected from all mothers prior to delivery, and cord blood is collected from all infants at delivery (*N* = 338 mother/infant pairs). Blood samples are also collected from a subset of 72 mother/infant pairs at 6 months postpartum, and 260 infants at 12 months postpartum. Reduced sample sizes at 6 and 12 months postpartum are related to time and budget constraints. These sample sizes will allow us to examine whether mother/infant biologic metrics are correlated at each time point and to build predictive models for infant biologic outcomes. Additionally, *n* = 72 mother/infant pairs with baseline and 6-month follow up will allow us to detect meaningful differences in the related biometric measures by maternal characteristics and/or maternal/infant behaviors (standardized mean detectable differences = 0.68), taking into account 4% loss-to-follow-up at 6 months postpartum (based on previous Family Spirit trials) and ensuring 80% power and significance level of 5% [69]. Finally, a sample size of *n* = 260 infants at 12 months will allow us to detect meaningful between intervention group differences in infant biometric outcomes (standardized mean detectable differences = 0.38), taking into account 16% loss to follow-up at 12 months postpartum and ensuring 80% power and a significance level of 5%.

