#### Primary aims analysis

We will conduct intent-to-treat analyses to estimate effects of the FSN + OSC intervention compared to the OSC + IPE control condition on early childhood obesity and related risk factors. Separately, we will examine the effects of intervention dose and conduct a “completer analyses” on subjects receiving minimum intervention dose (> 50% of lessons). Analyses will be adjusted for multiple comparisons using Bonferonni corrections.

Demographic and outcome variable distributions will be examined to assess whether comparability between intervention groups at baseline was achieved through randomization. For time discrete outcome measures, t- tests or chi-square tests will be used to test whether the intervention impacted each outcome in unadjusted analyses. Multiple linear or logistic regression will be used to test the impact of the intervention on each outcome, controlling for baseline demographic characteristics where necessary and examining potential moderators in secondary analyses. For time varying outcome measures we will examine the impact of the intervention by analyzing between group differences at each time point using t-tests and multiple regression analyses. For those outcomes with sufficient power, multi-level mixed-effects regression with a random effect at the individual level and appropriate variance structures, and an interaction term for treatment x child age will be used to examine change over the course of the intervention period for the intervention and control groups.

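### Table 3 claims at least 80% power at an uncorrected 5% level per outcome, but the analysis applies Bonferroni, so power for those differences falls below 80%: about 55–56% if the six sized outcomes form the family

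*Protocol article*

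**What the plan says.** Under Sample size calculation and statistical analysis, the protocol article says: "Sample size was powered to detect meaningful differences between the intervention (FSN + OSC) and control group (OSC + IPE) across six primary outcomes". It puts the total at 338, 169 in each arm. Attrition is allowed for by "taking into account an estimated 16% loss-to-follow-up at 24 months postpartum". The error rates are given as "ensuring at least 80% power and significance level of 5" per cent. On method it says "Sample sizes and power were calculated using Stata 13’s power command (two means for continuous variables and two proportions for binary variables"; the BMI z-score alone was handled by simulation from site data. Table 3 gives the detectable differences: 14 points for breastfeeding initiation, 15 points for exclusive breastfeeding, 23 days for duration, 13 points for introduction of sugar-sweetened beverages (SSBs), five feeding subscales at "0.20 points 0.24 points 0.22 points 0.20 points 0.32 points", and 0.33 SD for BMI z-score. That makes ten rows for six outcomes.

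Under Primary aims analysis the article then says: "Analyses will be adjusted for multiple comparisons using Bonferonni corrections". It gives no number of comparisons. The same section plans between-group tests at each time point for time-varying outcomes.

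**The concern.** A 5% level for each of six outcomes and a Bonferroni correction across outcomes are different tests with different critical values. If Table 3 was computed at 5% per outcome, its 80% belongs to a test that the analysis section says will not be used. Type I error is not at risk, because the correction protects it, and no estimate is biased. What is at stake is the meaning of a non-significant result. A reader who trusts Table 3 would take a null finding at 0.33 SD as coming from a test with 80% power, when the corrected test has materially less.

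**Working it through.** **Inputs.** From the sample size section: 169 per group, 16% loss at 24 months, 80% power, 5% level. Two-sided testing is assumed. Evaluable per arm: 169 × 0.84 = 141.96, taken as 142. The article does not state the control rates used. Two background figures are assumed in their place: 68.9% for initiation (Background, Breastfeeding) and 87% for SSBs by 12 months (Background, Sugar sweetened beverages).

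**Step 1. Reproduce Table 3 at an uncorrected 0.05.**
- BMI z-score: detectable d = (1.960 + 0.842) × √(2/142) = 0.3325. Table 3 prints 0.33. Power at exactly 0.33 SD is Φ(0.33 × √(142/2) − 1.960) = Φ(2.781 − 1.960) = 79.4%.
- Initiation, 68.9% vs 82.9%, two-proportion normal formula: power 79.1%; detectable difference 14.1 points. Table 3 prints 14.
- SSB introduction, 87% vs 74%, same formula: power 79.3%; detectable difference 13.1 points. Table 3 prints 13.

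**Step 2. Test the alternative that the 5% was already split six ways.** The critical value at 0.05/6 = 0.00833 is 2.638. The BMI row would then be (2.638 + 0.842) × √(2/142) = 0.413 SD, not 0.33. Initiation would be about 17.2 points, not 14, and SSB introduction about 16.9 points, not 13. The BMI comparison needs no assumed control rate and is enough by itself.

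**Step 3. Power of the corrected test.** For an outcome sized at exactly 80%, power after Bonferroni over m tests is Φ(1.960 + 0.842 − z), where z is the two-sided critical value at 0.05/m. The BMI column uses 0.33 SD and 142 per arm.

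| m | z | sized at exactly 80% | BMI z-score |
|---|---|---|---|
| 1 | 1.960 | 80.0% | 79.4% |
| 2 | 2.241 | 71.2% | 70.5% |
| 3 | 2.394 | 65.8% | 65.0% |
| 6 | 2.638 | 56.5% | 55.7% |
| 10 | 2.807 | 49.8% | 48.9% |

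At m = 6 and 142 per arm, initiation has 54.8% and SSB introduction 55.1%, both under the assumed control rates.

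**Step 4. Sensitivity to attrition.** Initiation is known early. The biologic sample size text gives 4% loss at 6 months, so 169 × 0.96 = 162 per arm; initiation then has 62.2% at m = 6. With no loss at all (169 per arm), BMI has 65.4% at m = 6.

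**Not checkable.** Breastfeeding duration and the five subscales have no SD in the article, and exclusive breastfeeding has no control rate. The third column of the table applies to those rows only if they sit at 80%.

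**The case against.** The strongest reply is that the article does not define the Bonferroni family, so no single power figure can be asserted. Defining it is commonly left to a full protocol or analysis plan, neither of which is shown. This stands against any fixed figure, and against treating 56% as an upper bound: two tests would give 71%. It does not rescue the claim, because every family larger than one takes power below 80%. Nor is this an omission: the article itself states both the power and the correction, and they do not agree.

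A second reply is that 142 per arm applies 24-month loss to every outcome, and that the planned regression and mixed models may be more efficient than two-sample tests. The first part stands for early outcomes, as the 62% for initiation shows. The gain from modelling is possible, but the documents give no amount for it.

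A third is that the power claim reads as a minimum, which leaves slack. The three rows that can be checked lie at 79–80% and have none, although two of them rest on assumed control rates.

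A reader might go further and infer that every primary outcome has about an even chance of success, or that the trial is too small and must be enlarged. The documents support neither. The first needs a particular family, 24-month attrition throughout and rows that cannot be verified. The second does not follow, because N = 338 can stand with restated detectable differences.

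**Conclusion.** The point holds as an inconsistency between the sample size section and the analysis section. Table 3 reflects an uncorrected 5% per outcome: the BMI z-score row shows this without any assumed rate, and initiation and SSB introduction agree under assumed control rates. Under the stated Bonferroni correction, power for the Table 3 differences is below 80% for any family of more than one test, for outcomes sized at 80%. For the six outcomes of the sample size section, at 142 evaluable per arm and with unadjusted two-sample tests, it is about 55–56%. The detectable BMI z-score difference at 80% power becomes about 0.41 SD, and initiation and SSB introduction each become about 17 points. Bonferroni is a valid choice and is not itself the error.

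**What to change.** Under Primary aims analysis, state which comparisons form the Bonferroni family: which outcomes, which time points, and how the five feeding subscales count. Reconcile that family with the Primary outcomes section, which also lists accelerometry, reported physical activity and screen time, and fruit and vegetable intake, none of which appear among the six outcomes used for sizing. Then either recompute Table 3 at the corrected level, or keep the present differences and state the reduced power beside them, using each outcome's own expected loss.

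The cost is wording and recalculation. With a six-test family the BMI z-score difference grows by about 24% (0.413/0.3325 = 1.24), and no participants are added. Holm in place of single-step Bonferroni is an optional gain: it controls the same familywise error and never rejects less. It is not needed to correct the inconsistency.

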## Methods/design

### Trial design

This study is a two-arm randomized controlled trial (RCT) with primary endpoints of parent feeding practices, young children’s diet and PA, and early childhood (0–2 years of age) weight status. Stratified block randomization with a 1:1 allocation is used to ensure equal allocation to intervention and control groups across key maternal baseline characteristics (Fig. 1).

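### Bonferroni is a valid multiplicity adjustment here, but for testing it is dominated by Holm's step-down procedure; switching is an optional efficiency gain

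*Protocol article*

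**What the plan says.** The Primary aims analysis section of the protocol article settles multiplicity in one sentence: "Analyses will be adjusted for multiple comparisons using Bonferonni corrections". It gives no algorithm, does not list the family, and offers no reason for single-step testing, such as a wish for simultaneous confidence intervals. Plain Bonferroni is the natural reading.

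The section Sample size calculation and statistical analysis describes the trial as "powered to detect meaningful differences between the intervention (FSN + OSC) and control group (OSC + IPE) across six primary outcomes", with the calculation "ensuring at least 80% power and significance level of 5" per cent. The six are three breastfeeding measures, introduction of sugar-sweetened beverages, the responsive feeding scale and BMI z-score. Table 3 splits the feeding scale into five subscales. The analysis section also plans group comparisons at each time point for outcomes that vary over time.

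**The concern.** Single-step Bonferroni tests each of m outcomes at alpha/m, however many of the others have already been rejected. Holm orders the p-values and tests the smallest at alpha/m, the next at alpha/(m−1), and so on up to alpha, stopping at the first failure. Its first threshold equals Bonferroni's and every later one is larger. It therefore cannot reject less, and it needs no extra assumption about dependence.

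The difference shows only when several outcomes respond. This trial hopes for that: the intervention section sets out to change breastfeeding, complementary and responsive feeding, diet, activity and weight together. What is at stake is a real effect on a further outcome being reported as not significant when an equally valid family-wise procedure would have declared it.

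**Working it through.** **Inputs from the protocol article**
- Sample size: "A sample size of 338, or 169 per group, was deemed sufficient to detect meaningful differences across all outcomes"; loss: "an estimated 16% loss-to-follow-up at 24 months postpartum". Evaluable per group: 169 × (1 − 0.16) = 141.96, about 142.
- Level and power: 5% and 80%, with no adjustment mentioned.
- Family: m = 6, from "across six primary outcomes". Counting the five feeding subscales separately gives 5 + 5 = 10.
- Detectable difference for BMI z-score (Table 3): 0.33 SD.

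**Assumptions.** Two-sided tests (sidedness is not stated), the same standardised effect on every outcome that responds, and equal correlation of 0 or 0.3 between outcomes.

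**1. The plan's own figure.** Detectable difference = (z₀.₉₇₅ + z₀.₈₀) × √(2/n) = (1.960 + 0.842) × √(2/142) = 2.802 × 0.1187 = 0.3325 SD. The article obtained its 0.33 by simulation, and the formula agrees at an unadjusted two-sided 5%.

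**2. Thresholds for m = 6.** Bonferroni uses 0.05/6 = 0.0083 throughout. Holm uses 0.0083, 0.0100, 0.0125, 0.0167, 0.0250 and 0.0500 in turn.

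**3. Bonferroni power per true effect.** An outcome with 80% unadjusted power has noncentrality 2.802. The critical value at 0.05/6 two-sided is 2.638. Power = Φ(2.802 − 2.638) = Φ(0.163) = 0.565.

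**4. Holm against Bonferroni by simulation.** 200,000 sets of six z-statistics, noncentrality 2.802 for each real effect, correlation 0:

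| Real effects among six | Bonferroni, average power | Holm, average power | Gain (points) |
|---|---|---|---|
| 1 | 0.565 | 0.567 | about 0 |
| 2 | 0.565 | 0.580 | 1.5 |
| 3 | 0.565 | 0.597 | 3 |
| 4 | 0.565 | 0.618 | 5 |
| 6 | 0.565 | 0.683 | 12 |

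At correlation 0.3 every figure is within one point (six real effects: about 0.675). The chance of at least one rejection is identical for the two methods. Holm declares at least one additional outcome in about 10% of trials with three real effects, 19% with four and 48% with six. Taking exactly 0.33 SD and 142 per group, where unadjusted power is 0.79, gives the same pattern: 0.56 against 0.59 (three real) and 0.67 (six real).

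**5. Family-wise error.** With no real effect it is about 0.049 for both methods at correlation 0. With at least one real effect it was at or below about 0.046 for Holm.

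**6. Larger families.** With three real effects, the gain is about 1.5 points at m = 10 and 0.5 points at m = 20. If all ten of ten effects are real, a gain of about 11 points remains.

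**The case against.** The strongest reply is that nothing here is wrong. Bonferroni is standard, valid and pre-specified, and choosing another valid method is close to preference. The source is a condensed article, and an analysis plan that is not shown may say more. This stands as far as weight goes: the point concerns efficiency only. It does not remove the point, because the article does name the procedure.

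A reader might infer that Bonferroni's strictness buys nothing. That is not so. It also caps the expected number of false rejections at alpha, which Holm does not: with six true nulls at correlation 0.7 the expected numbers are 0.049 and 0.059. With five real effects of the assumed size, the false-positive rate on the sixth, null outcome rises from about 0.9% to 2.4%. If those five are strong enough always to be rejected, it rises from 0.05/6 = 0.83% to the full 5%. Family-wise error is still held at 5%, but protection of each single outcome is weaker. Bonferroni also has simple simultaneous intervals that match its tests, which matters in a section that sets out to estimate effects.

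Timing is a further cost. The outcomes mature from the early postpartum weeks to 24 months. Bonferroni lets each be judged at a fixed threshold when it is ready. Under Holm, an early outcome that misses alpha/m may have to wait for the rest of the family. The article gives none of these as its reason, but they are real.

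**Conclusion.** For hypothesis testing at a given family-wise error rate, Holm dominates the Bonferroni adjustment fixed in the article. That holds for any family size and any dependence. The size of the gain does rest on assumptions: six outcomes, two-sided tests, equal effects each with 80% unadjusted power, and modest correlation. On these, average power per true effect rises from about 56.5% to 58% with two real effects, 60% with three and 62% with four. The 68% figure requires all six effects to be real, BMI z-score included, and should not be quoted as the expected benefit.

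Two stronger readings are tempting. One is that the choice of Bonferroni is an error in type I control. The documents do not support this, since Bonferroni controls it. The other is that Holm would repair the gap between a sample size reckoned at an unadjusted 5% and an adjusted analysis. It would not: even 68% is short of 80%. Under Bonferroni over six outcomes, 80% power at 0.33 SD would need 223 evaluable per group, or 223/0.84, about 266, randomised per group against the planned 169. This is an optional improvement.

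**What to change.** For the primary family, replace the Bonferroni wording with Holm's step-down procedure at two-sided 5%, fixed before any unblinded outcome comparison, and report Holm-adjusted p-values. Then either state that any unadjusted 95% intervals are not matched to the Holm decisions (an interval may exclude zero where Holm does not reject), or give Bonferroni-simultaneous intervals. The family has to be listed, and decisions on outcomes that miss the first threshold must wait until all the p-values that could affect them are available.

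No extra participants or data are needed. The cost is a wording change, submitted as an amendment to the relevant review boards as the article's ethics section requires for protocol modifications, together with the looser per-outcome error and the less simple matching intervals. If the sponsor prefers Bonferroni for its intervals or its fixed thresholds, one sentence giving that reason would settle the point.

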### Randomization

Participants are individually-randomized to receive the intervention or control program. Randomization is completed after the completion of the baseline assessment. Randomization is stratified by age (< 18 years old and 18 years and older), site, and food and water security status. Randomization lists for each site were created and uploaded to REDCap prior to study initiation using STATA 14 statistical software [61]. The randomization lists are not accessible by study staff. After baseline is complete, the field coordinator verifies baseline data and randomizes the participant in REDCap. Study staff are then informed of the participant’s study allocation. This is locked and unchangeable within REDCap.

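### Randomisation is stratified by age group, site and food/water security, but no stated analysis commits to adjusting for these factors, so any precision they offer is left to chance

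*Protocol article*

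**What the plan says.** The Trial design section states the purpose of the allocation scheme: "Stratified block randomization with a 1:1 allocation is used to ensure equal allocation to intervention and control groups across key maternal baseline characteristics". The Randomization section names the factors: "Randomization is stratified by age (< 18 years old and 18 years and older), site, and food and water security status".

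The Primary aims analysis section describes four kinds of analysis:

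- For outcomes measured once, "t- tests or chi-square tests will be used to test whether the intervention impacted each outcome in unadjusted analyses".
- Linear or logistic regression for each outcome, "controlling for baseline demographic characteristics where necessary and examining potential moderators in secondary analyses". This comes after baseline distributions have been examined "to assess whether comparability between intervention groups at baseline was achieved through randomization".
- For time-varying outcomes, "analyzing between group differences at each time point using t-tests and multiple regression analyses".
- Where power allows, "multi-level mixed-effects regression with a random effect at the individual level and appropriate variance structures", with a treatment by child age interaction.

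None of the four names the stratification factors as covariates. Food/water insecurity does appear in the Sample size calculation and statistical analysis section, but as a hypothesised moderator, not as a main-effect adjustment.

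**The concern.** Stratified blocks remove most of the between-stratum variation from the difference between arms. A t-test or chi-square test that ignores the strata still counts that variation as noise. If the strata predict the outcome, the test rejects less often than 5% under the null and its confidence interval is wider than it needs to be.

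The regressions could put this right, but the covariate rule works against it. It is conditional, it follows a balance check, and it refers to demographic characteristics. Factors balanced by stratification will rarely look imbalanced, so a trigger based on imbalance tends to exclude the very variables that the design calls for. Age would count as demographic and site might; food/water security is not plainly so. An undefined condition also leaves the covariate set open to choice after the data have been seen.

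At stake is some forgone precision on the primary outcomes, together with a looser specification than the design supports. There is no bias and no excess of false positives.

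**Working it through.** **Inputs from the article.** 338 mothers, 169 per arm; 16% loss to follow-up at 24 months; 80% power; 5% significance (Sample size calculation and statistical analysis). Detectable BMI z-score difference 0.33 SD (Table 3).

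**Assumptions.** Two-sided testing. The share of outcome variance explained by the strata, R², is not given, so 0 to 20% is examined.

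**Step 1: the plan's own figure.** Evaluable per arm: 169 × 0.84 = 141.96, or 142. The standard error of the difference in SD units is √(2/142) = 0.1187. The detectable difference at 80% power is (1.960 + 0.842) × 0.1187 = 0.332 SD, and power at 0.33 SD is 79.4%. The article obtained its BMI figure by simulation, but the plain two-sample formula gives the same answer, with no allowance for strata.

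**Step 2: effect of ignoring the strata.** Let s = √(1 − R²), c = 1.960 and m = 0.33 / 0.1187 = 2.78. With the strata balanced across arms, the true standard error is s times the one the t-test uses. Then, with Φ the normal distribution function:

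- True type I error of the unadjusted test = 2 × [1 − Φ(c/s)]
- Power, unadjusted = Φ((m − c)/s)
- Power, strata in the model = Φ(m/s − c)

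| R² (assumed) | Unadjusted SE too large by | True type I error, unadjusted | Power, unadjusted | Power, adjusted | Gain (points) |
|---|---|---|---|---|---|
| 0 | 0% | 5.0% | 79.4% | 79.4% | 0 |
| 2% | 1.0% | 4.8% | 79.6% | 80.2% | 0.6 |
| 5% | 2.6% | 4.4% | 80.0% | 81.4% | 1.4 |
| 10% | 5.4% | 3.9% | 80.6% | 83.4% | 2.8 |
| 20% | 11.8% | 2.8% | 82.1% | 87.5% | 5.4 |

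Example at R² = 10%: s = 0.949; c/s = 2.066, giving 3.9%; (2.78 − 1.96)/0.949 = 0.865, giving 80.6%; 2.78/0.949 − 1.96 = 0.971, giving 83.4%.

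Unadjusted power also rises with R², because balance reduces the real variability of the estimate. The gain must therefore be measured against the unadjusted column in the same row, not against a fixed 80%.

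**Step 3: simulation check.** The set-up was 284 evaluable mothers, 12 strata (three sites, two age groups and a two-level security factor, the last an assumption), blocks of four (also assumed) and 8,000 runs per setting. Unadjusted type I error was 4.8%, 3.7% and 3.2% at R² of 5%, 10% and 20%. Power, unadjusted against adjusted, was 79.6% and 80.7%, 80.4% and 83.3%, and 81.4% and 87.0%. This agrees with the table to within about 0.7 points.

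**Scope.** The table applies to continuous outcomes. A figure for the binary outcomes would need outcome rates by stratum, which the article does not give.

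**The case against.** The strongest reply is that the sentence on t-tests and chi-square tests calls its own analyses unadjusted, and that the next sentence gives every outcome a regression. The article does not say that the unadjusted test is the primary one. A reader might infer that the strata necessarily drop out of the analysis. The text does not support that: age, and perhaps site, could enter as demographic characteristics. What stands is that no analysis commits to them, and that food/water security is not clearly covered at all.

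A second reply is that covariate lists usually belong in the analysis plan, which is not shown. That would settle the matter if the article were silent. It is not: it states a rule, and the rule suits this design badly. An analysis plan that named the strata would supersede the rule without conflicting with the rest of the article.

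Two further readings are tempting and should be resisted. One is that power built into the design is being lost. The sample size used two-mean and two-proportion formulas, with a simulation for BMI z-score that describes random assignment but no strata. No stratification gain was budgeted, and unadjusted power stays at 79.4% to 82.1% across the range examined. The other is that standard errors are too large throughout. In logistic models, adjustment targets a conditional odds ratio and usually raises its standard error; the benefit there is in power.

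It is also true that the size rests wholly on an assumed R². If the strata explain about 2% of variance, the effect is negligible.

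**Conclusion.** The point holds in a limited form. The design stratifies on three factors, and the stated analysis rule neither names them nor is likely to pick them up. If the strata are prognostic, the unadjusted tests are conservative, with a true type I error of about 4.4%, 3.9% or 2.8% at an R² of 5%, 10% or 20%. For a continuous outcome at 0.33 SD with 142 per arm, the power forgone is about 1.4, 2.8 or 5.4 points, and 0.6 at an R² of 2%. These figures assume two-sided 5% testing, near-balance within strata among mothers followed up, and R² values that the article does not supply. The trial's validity and its planned 80% power are not in question. This is an inexpensive improvement in precision, and it removes an undefined choice of covariates.

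**What to change.** In the Primary aims analysis section, or in the analysis plan:

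1. Name age group (under 18, or 18 and older), site and food/water security status as fixed covariates in every primary linear, logistic and mixed model. For proportions, a Cochran-Mantel-Haenszel test across the strata is an alternative.
2. Remove the where-necessary condition for these three factors, so that their inclusion does not depend on a baseline balance check.
3. Label the unadjusted t-tests and chi-square tests as supportive.
4. For the logistic models, state that the adjusted odds ratio is conditional on the strata, so that its standard error is not compared directly with the unadjusted one.

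The cost is a few sentences. The factors are known before allocation because they drive the randomisation, so no new data are needed. With three sites and a two-level security factor (the number of levels is an assumption), main effects use 1 + 2 + 1 = 4 degrees of freedom, which is trivial against 284 evaluable mothers. The change should be fixed before outcome data are examined by arm.

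### Randomisation is stratified by age group, site and food/water security, but no planned model commits to these factors and covariate adjustment is left conditional after a balance check

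*Protocol article*

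**What the plan says.** Under Randomization the article states: "Randomization is stratified by age (< 18 years old and 18 years and older), site, and food and water security status". Under Primary aims analysis, the relevant paragraph begins with an examination of whether randomisation produced comparable groups at baseline. It then sets out three kinds of analysis:

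- For outcomes at a single time, t or chi-square tests "will be used to test whether the intervention impacted each outcome in unadjusted analyses", and linear or logistic regression "controlling for baseline demographic characteristics where necessary".
- For time-varying outcomes, between-group comparisons at each time point, by t-tests and by multiple regression.
- A longitudinal model for some outcomes only: "For those outcomes with sufficient power, multi-level mixed-effects regression with a random effect at the individual level", with a treatment by child age interaction.

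No section names the stratification factors as covariates, and none says which of these results is the main estimate. In the sample size section, food/water insecurity appears as a hypothesised moderator.

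**The concern.** Stratified blocks force the arms to be nearly balanced on age group, site and food/water security. If these factors predict the outcome, the difference in means varies less from one randomisation to the next than an unadjusted standard error assumes. P-values are then too large on average, intervals are too wide, and precision that the design has already bought is not used.

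The covariate rule raises a separate problem. It is conditional, it covers demographics only, and it comes after a balance check in the same paragraph. The natural reading is that observed imbalance decides what is adjusted for, so the model for the effect would depend on the data. Reserving the mixed model for outcomes with enough power adds another choice. It also limits use of the one planned method that draws on all available visits.

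**Working it through.** **Inputs from the article.** "A sample size of 338, or 169 per group"; "an estimated 16% loss-to-follow-up at 24 months postpartum"; "ensuring at least 80% power and significance level of 5"% (two-sided assumed); power from "two means for continuous variables and two proportions for binary variables", except BMI z-score, which was simulated; detectable BMI z difference 0.33 SD (Table 3).

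**Assumed input.** R², the share of outcome variance explained by the three factors. The article does not give it, so a range of 0 to 0.30 is shown.

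**Step 1: the plan's own figure.** Analysed per arm: 169 × 0.84 = 142. Detectable difference: (1.960 + 0.842) × sqrt(2/142) = 0.333 SD, which matches 0.33. In the other direction, 0.33 SD needs 145 per arm. Dividing by 0.84 gives 173 per arm, 346 in total, within 3% of 338. The stated size therefore reproduces as an unadjusted two-group comparison. Power at 0.33 SD with 142 per arm is 79.4%.

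**Step 2: effect of ignoring the strata.** Let s = sqrt(2/142) = 0.1187, so 0.33/s = 2.781. With the strata balanced, the true standard error is s × sqrt(1 − R²), while the unadjusted test uses s.

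- True size, unadjusted: 2 × [1 − Φ(1.96/sqrt(1 − R²))]
- Power, unadjusted: Φ((2.781 − 1.96)/sqrt(1 − R²))
- Power, adjusted: Φ(2.781/sqrt(1 − R²) − 1.96)
- Detectable difference, adjusted: 2.802 × s × sqrt(1 − R²)

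| Assumed R² | Unadjusted true size | Unadjusted power | Adjusted power | Gain (points) | Adjusted detectable difference (SD) |
|---|---|---|---|---|---|
| 0 | 5.0% | 79.4% | 79.4% | 0 | 0.332 |
| 0.05 | 4.4% | 80.0% | 81.4% | 1.4 | 0.324 |
| 0.10 | 3.9% | 80.6% | 83.4% | 2.8 | 0.315 |
| 0.20 | 2.8% | 82.1% | 87.5% | 5.4 | 0.297 |
| 0.30 | 1.9% | 83.7% | 91.4% | 7.7 | 0.278 |

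**Step 3: simulation check.** Assumed set-up: 12 strata, blocks of 4, 284 analysed; 6,000 runs under no effect and 3,000 at 0.33 SD. For R² of 0.05, 0.10 and 0.20:

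- Unadjusted size 4.5%, 3.9%, 3.3%; adjusted size 4.9%, 5.0%, 5.4%.
- Unadjusted power 78.9%, 81.1%, 81.5%; adjusted power 80.4%, 83.7%, 88.1%.
- Taking the smaller of the two p-values gave a size of 5.0%, 5.0%, 5.4%.

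The direction and rough size agree with the formulas. The last line shows that choosing between these two tests alone hardly raises the error rate. Selection from a wider covariate list was not simulated.

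**Step 4: which outcomes have a baseline value.** The six powered outcomes are ever breastfed, exclusive breastfeeding, breastfeeding duration, sugar-sweetened beverage introduction, responsive feeding and child BMI z-score. All are first measured after birth, hence after randomisation. Table 2 shows baseline measurement of maternal stress, depression and ASSIST, which are secondary outcomes.

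**The case against.** The best reply is that this is a condensed article. A full protocol exists, an analysis plan may exist, and a covariate list usually belongs there. Age is itself a baseline demographic, so the text does not exclude it, and it never says outright that imbalance decides adjustment. This has force: the mere absence of a list would be no finding. What stands is the rule that the article does state, namely unadjusted tests plus conditional adjustment, in a trial whose stratification factors are already fixed.

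Several stronger readings are tempting but unsupported:

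- **Effects rest on unadjusted per-visit tests alone.** They do not. Regression is planned for outcomes at a single time and at each time point for time-varying ones, with mixed models for some.
- **Baseline values of the main outcomes are ignored.** The six powered outcomes have none, so any gain from baseline adjustment concerns maternal secondary measures only.
- **The per-visit analyses are complete-case and drop 16%.** The article does not call them complete-case, and 16% is the 24-month loss estimate behind the total sample size.
- **Adjusted power should be compared with a fixed 80%.** That overstates the gain, because the unadjusted test's power also rises under stratified allocation, as the table shows.
- **The trial is anti-conservative or undersized.** Ignoring the strata errs in the conservative direction, and 338 is unaffected.

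**Conclusion.** The point holds as a matter of efficiency and prespecification. As written, the unadjusted tests run at a true size of about 4.4% to 2.8% instead of 5%, and give up about 1.4 to 5.4 points of power for a continuous outcome, at an assumed R² of 0.05 to 0.20. At R² = 0 there is no loss. The figures use a nominal two-sided 5% level, 142 analysed per arm and near-exact balance within strata. They do not carry over to the three binary powered outcomes. The openness of the covariate choice is a defect of the wording, and its effect on error rates has not been quantified. That imbalance will drive the choice is the natural reading, not an explicit statement.

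**What to change.** 1. For each outcome, make the main estimate a linear or logistic regression with treatment, age group, site and food/water security as fixed covariates, coded as used at randomisation.
2. For repeated outcomes, use one mixed model on all available visits with the same covariates. For BMI z-score, report its 24-month contrast, which is the quantity the sample size section powers.
3. Add the baseline value only for maternal outcomes that have one: stress, depression and ASSIST.
4. Remove the necessity condition on adjustment and the sufficient-power condition on the mixed model.
5. Keep the t and chi-square tests as descriptive.

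The cost is wording in the analysis plan. The stratification factors are known before allocation and the maternal baseline measures are already scheduled, so no extra data or participants are needed.
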